### Endpoints

At the end of the study two endpoints will be evaluated:

1. Successful Treatment:

a. Complete reepithelization three months after the beginning of the treatment.

b. Absence of reactivation and affections of the mucous membranes during the 6 months of the study.

2. Treatment Failure:

a. Incomplete reepithelization three months after the beginning of the treatment.

b. Increase in the size of the ulcer by more than 50% in relation to the last clinical evaluation

c. Reactivation and/or affections of the mucous membranes during the 6 months of the study.

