#### Recruitment phase

This phase will take 22 months. In the selected municipalities, the health personnel that work in hospitals and health centers will receive training regarding the disease and the study methodology. Simultaneously an epidemiological focus study will be done with the leaders of the community and the health personnel to identify the geographic and demographic conditions with the purpose of developing strategies for the recruitment of possible cases of leishmaniasis. Subsequently, the subjects that present active ulcers with more than 2 weeks of evolution, with or without parasitological confirmation of CL, will be invited by the health promoters to attend the screening visit (Table 1).

**Table 1 T1:** Schedule of activities

**PROTOCOL ACTIVITIES**	**Screening Visit**	**Initial Visit**	**Treatment visits**	**Follow-up visits**			
				**Visit 1**	**Visit 2**	**Visit 3**	**Visit 4**
**SCHEDULE OF VISITS**		0	1–20	21+3	45 ± 7	90 ± 14	180 ± 14
Clinical History	X	X		X	X	X	X
Physical Examination	X	X		X	X	X	X
Inclusion/Exclusion criteria	X						
Informed Consent	X						
Direct test	X						
Sampling of cultures		X					
Laboratory tests		X		X			
Randomization		X					
Treatment administration		X	X				
Clinical assessment of the lesion	X	X	X	X	X	X	X
Measurement of ulcers		X		X	X	X	X
Photographic registration		X		X	X	X	X
Education of patients	X	X	X	X	X	X	X
Handing over of diary		X					
Evaluation of effectiveness				X	X	X	X
Documentation of adverse events	X	X	X	X	X	X	X
Recording of concomitant medications	X	X	X	X	X	X	X

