### Follow-up visits

This phase will last 10 months. During the follow-up, the patients will be seen by the research group in 4 opportunities. The first visit will take place the day after the end of the treatment (day 21) in which new blood samples will be taken for biochemical determinations. The second, third and fourth visits will be realized on day 45, 90 and 180 respectively. During these visits the healing process of the ulcer, the presence of recidivisms and/or reinfection and the health of the participants will be assessed. The evolution of the ulcers will be photographically registered.

The maximum and minimum diameters of the ulcer will be measured using a graduated ruler, and the induration using the ballpoint pen technique. The ulcer and induration areas will be calculated separately, and then registered in the CRF. The evaluation of the clinical response will be based on the ulcer showing the least improvement.

1. Complete clinical response: Complete reepithelization of the ulcer and disappearance of the induration.

2. Clinical Improvement: Reduction of more than 50% of the ulcer and the induration areas in relation to the last clinical evaluation.

3. Absence of clinical response: Increase or reduction of less than 50% of the ulcer and the induration areas in relation to the last clinical evaluation.

4. Therapeutic failure:

a. Increase in the size of the ulcer by more than 50% in relation to the last clinical evaluation

b. Presence of the ulcer three months after the beginning of the treatment.

c. Reactivation: Appearance of a lesion on the edge or in the center of the scar, with positive parasitological diagnosis, after a period of complete reepithelization.

d. Affection of the mucous membranes: Presence of affections of the mucous membranes during the treatment, at the end of it or in the follow-up visits.

5. Reinfection: Activation of an ulcer in an area different from the original lesion.

For subjects whose treatment will have been considered a failure the code will be broken and they will be remitted to their original health center to look for other therapeutic approach.

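### Success and failure overlap: an ulcer that grows by more than 50% at day 21 or 45 and is closed at day 90 meets both definitions

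*Protocol article*

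**What the plan says.** The Endpoints section gives two lists.

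- Success needs 1a, "Complete reepithelization three months after the beginning of the treatment", and 1b, "Absence of reactivation and affections of the mucous membranes during the 6 months of the study".
- Failure is 2a, "Incomplete reepithelization three months after the beginning of the treatment"; or 2b, "Increase in the size of the ulcer by more than 50% in relation to the last clinical evaluation"; or 2c, reactivation or mucosal involvement within the six months.

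The section says that both endpoints are evaluated at the end of the study. It does not say which list governs if a patient fits both.

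The Follow-up visits section repeats the growth clause as therapeutic failure 4a. It adds that for failures "the code will be broken and they will be remitted to their original health center to look for other therapeutic approach". The same section has the largest and smallest diameters measured with a ruler and areas calculated from them, and judges response on the ulcer that has improved least.

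In Table 1 the row "Measurement of ulcers" is marked at day 0 and at the day 21, 45, 90 and 180 visits. At the daily treatment visits the lesion is assessed clinically but no measurement is scheduled.

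**The concern.** A binary endpoint has to place each patient in exactly one class. Here one failure clause has no counterpart under success, so some patients can be placed in both. The choice for them is left to whoever does the analysis, in a trial that asks whether the patch is at least as effective as antimony, breaks the code for failures and plans two interim looks.

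The referral rule adds to this. A patient who meets the growth clause at day 21 or 45 is referred for other treatment. If that patient comes back for the day-90 visit with a closed ulcer, the success definition as printed is met, although the healing may be due to the other treatment.

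The clause itself is also loosely fixed. Size may mean area or diameter, the reference is the previous evaluation, and there is no minimum size. A small ulcer that rebounds slightly can therefore count as a failure.

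**Working it through.** **1. Are the two lists complementary?**

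| Success | Matching failure | Complement? |
|---|---|---|
| 1a, closed at three months | 2a, not closed at three months | yes |
| 1b, no reactivation or mucosal disease to six months | 2c, reactivation or mucosal disease | yes |
| none | 2b, growth above 50% since the previous evaluation | no counterpart |

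Without 2b, failure is exactly the negation of success. With 2b, the overlap is the set of patients with 1a and 1b and 2b all true.

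**2. When can the overlap occur?**

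- Day 90: an open ulcer already fails under 2a, so 2b adds nothing.
- After day 90, ulcer closed at day 90: the last size is zero and a percentage increase is undefined.
- Day 21 or day 45: a measured increase above 50%, then closure at day 90 and no reactivation, gives 1a, 1b and 2b together.

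So the clause has a separate effect only before day 90, in practice at the day 21 and day 45 visits.

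**3. What does 50% growth mean?** For a round ulcer going from diameter d1 to d2, the change in area is (d2/d1)² − 1 and the change in diameter is d2/d1 − 1.

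| Previous to current (mm) | Area | Diameter |
|---|---|---|
| 2x2 to 3x3 | (3/2)² − 1 = +125% | +50%, not above 50% |
| 3x3 to 4x4 | (4/3)² − 1 = +78% | +33% |
| 4x4 to 5x5 | (5/4)² − 1 = +56% | +25% |

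All three are failures if size is area, and none is if size is diameter. In general, +50% in area is √1.5 − 1 = +22% in diameter, and +50% in diameter is 1.5² − 1 = +125% in area.

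Read as area, a rise of 1 mm in both diameters exceeds the limit for any round ulcer below 1/(√1.5 − 1) = 4.4 mm. Both diameters must move in the same direction: 3x3 to 3x4 mm is only 12/9 − 1 = +33%.

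Illustration: 20x20 mm at day 0, 3x3 at day 21, 4x4 at day 45. Read as area, this is +78% on the previous visit and a failure under 2b, with 16/400 = 4% of the entry area left.

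**4. How much could it matter?** The plan gives no frequency for the overlap, so there is no figure of its own to reproduce. The planning rates in the Sample size section are 85% and 75%, a difference of 10 points. Let a and p be the percentages of antimony and patch patients in the overlap. Suppose the planning rates count them as successes. Recounting them as failures gives (85 − a) − (75 − p) = 10 + (p − a).

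Assume p = 2-5% and a = 1-2%:

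- smallest shift: 2 − 2 = 0 points
- largest shift: 5 − 1 = 4 points, so a difference of 14 instead of 10
- with the two ranges swapped between arms, the shift is 0 to −4 points, so a difference as low as 6

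**The case against.** The strongest reply is that precedence is implied. The Follow-up visits section treats the same growth as therapeutic failure, breaks the code and sends the patient elsewhere, which reads as a terminal outcome. An article may also leave the operational rule to a fuller document. The first part has force: failure as the final status is the natural reading. But neither section says that an early failure overrides closure at day 90. Nor is this a detail left out by condensation, because both lists are printed and conflict as they stand.

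Several stronger conclusions are tempting, and the documents do not support them.

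- **That cures after referral will be counted as successes.** No section says whether referred patients return for the day-90 and day-180 visits. The point is conditional on their being assessed.
- **That nearly healed ulcers in general are scored as failures.** Only a small ulcer that rebounds by more than 50% before day 90 is caught, and the millimetre examples require size to mean area.
- **That growth at day 21 cannot be computed.** This needs the last evaluation to be the unmeasured day-20 visit, which is one reading. Day 0 is the last visit with a scheduled measurement and is at least as natural a reference.
- **That the response categories make the endpoint indeterminate.** The Follow-up visits section defines complete response as "Complete reepithelization of the ulcer and disappearance of the induration" and improvement as "Reduction of more than 50% of the ulcer and the induration areas in relation to the last clinical evaluation". An ulcer with a 60% and then a 40% reduction is thus labelled as no response at the second visit, though 0.4 × 0.6 = 24% of its area remains. These are visit-level categories that the Endpoints section does not use, and failure item 4b does not mention induration.
- **That the overlap pulls the arms together.** This presumes more early growth on the patch, for which no section gives evidence.

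**Conclusion.** The success and failure definitions in the Endpoints section are not mutually exclusive. This follows from the text alone and needs no outside figure. It affects patients with measured growth above 50% at day 21 or 45 whose ulcer is closed at day 90 without reactivation; everyone else is classified unambiguously by 2a, 2c and their complements, apart from the undefined meaning of size.

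The size of the effect is not known. Under the assumed overlap of 2-5% on the patch and 1-2% on antimony, the difference shifts by 0 to 4 points against 10 planned. The direction depends on which arm has more early growth, and the documents do not say. The case for a change rests on the contradiction and on how cheaply it can be removed, not on the upper end of that range.

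**What to change.** In the Endpoints section, define one binary endpoint in which failure takes precedence. Success is re-epithelialisation at the day-90 visit, and none of 2b or 2c, and no other anti-leishmanial treatment before the assessment. Everything else is failure. With this rule it no longer matters for the endpoint whether patients who meet the growth clause and are referred return for later visits.

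State whether size is the calculated area or a diameter, and that the reference is a visit at which Table 1 schedules a measurement.

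The growth clause and its reference should read the same in the Endpoints and Follow-up visits sections, and the investigators need to reconcile them. Changing the reference to day 0 for the analysis alone would separate the endpoint from the failure rule that triggers unblinding and referral, so it should not be done on one side only. No clinical threshold or referral rule is proposed here.

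The cost is wording in two sections, settled before the first interim analysis. Diameters and concomitant medications are already recorded at the visits concerned. The downside is that a few patients who healed after referral count as failures, so observed success rates may be slightly lower.

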### Final report

At the end of the study the results will be evaluated and discussed and a final report presented to COLCIENCIAS, entity that is sponsoring the project. The relevant results will be published in both, national and international journals, and presented in congresses and scientific meetings.

### Ethical aspects

This study will be conducted in accordance with the Declaration of Helsinki and with the Colombian legislation as per the Resolution 8430/93 from the Ministry of Health. Prior to the admission of the patients in the study, the objectives and the methodology will be explained and the informed consent obtained. The study was approved by the Research Ethic Committee of the Cardiovascular Foundation of Colombia (Act# 105/January 28/2005). The right to confidentiality of the patients will be maintained in all the phases of the study.
